## Results

The study is ongoing with enrollment underway since January 2019. Recruitment ended in January 2020, with extraction and linkage completed by March 2020. We expect the initial results for NHS Checks conducted between 2009 and 2018 and linked to Hospital Episode Statistics and Office for National Statistics to be published in mid-2021. This research has been supported by an unrestricted investigator-initiated research grant from Regeneron Pharmaceuticals to Imperial College London in 2015.

### Ethical Considerations

The study protocol underwent an external peer review before the ethics submission. This study has received a favorable ethics opinion by the East Scotland Research Ethics Committee (Ref: 17-ES-0104), Health Research Authority, and adopted by the clinical research network portfolio in November 2018.

## Discussion

Nationally delivered, the NHS Health Check program has the potential for universal outreach in the United Kingdom. However, differences in uptake of this program may lead to inadvertent and undesirable health inequalities (for instance, those already more likely to engage with the health care benefiting from increased contact while many who are less likely to engage with healthcare not availing themselves of this opportunity). However, it is unclear whether (and to what extent) ethnic differences at a population level drive such disparities, and whether targeting specific sociodemographic subgroups within the population might help mitigate CVD risk.

The complex interplay and variations of individual risk factors with wider determinants between and within regions and population groups reinforce the need for a detailed understanding of different cultural, socioeconomic, and epidemiological contexts for developing tailored population strategies.

Given its ethnic diversity (and a population of 8 million representing around 270 nationalities), London provides the ideal backdrop for studying CVD risk factor burden in all the permutations mentioned above. It has been estimated that the proportion of BME groups in London is 41% (10% in the rest of England). Moreover, a report commissioned by the King’s Fund found greater health inequalities in London than in the rest of England [13]. For instance, although CVD death rates are reported to be higher in the North than in the South of England, 10 of the 33 London boroughs are currently experiencing above-national-average mortality [26-28,30-37]. These factors highlight the need for a more in-depth understanding of the determinants of CVD risk based on ethnicity and other key demographic variables, which could then pave the way for more effective societal interventions.

Thus, the aim of our study, using NHS Health Check data in London, is to understand the burden of CVD risk factors and to eventually validate/develop ethnic-specific CVD risk prediction tools to inform public health policy and guidelines which could lead to improvements in overall health outcomes and reduction in healthcare costs.

Ethnic diversity in England in general, and London in particular, has hitherto not been systematically captured in large-scale studies creating uncertainty in the existing guidelines on CVD risk prevention. QRISK2 score has been shown to underpredict CVD risk in population groups such as South Asians, in part reflecting low representation of the ethnic groups in the cohorts to derive sufficient information to inform risk prediction tools adequately [40,41]. This disparity may be attributed to the low participation of GP practices in London who, based on the location of these populations, are likely to treat the greatest number of BME groups relative to the rest of England. Thus, in certain ethnic groups, there may be a missed opportunity to mitigate CVD risk as they are at greater risk of CVD but have a systematic under-estimation/-representation of risk. Given that EHR data in many GP practices within London have not been utilized for investigating CVD across the multiethnic population they serve, there is a unique opportunity to recruit these practices to share their EHR data and link with other EHR sources to create a registry of varied population groups.

Moreover, the data from this study could help develop bespoke risk prediction models across diverse ethnic groups that can be embedded into the existing GP EHR systems. Following the development of such models, individuals of diverse ethnicities could potentially be reclassified into higher- or lower-than-predicted CVD risk categories, thereby enabling more tailored approaches to prevention or intervention. By contrast, if conventional risk factors were found not to be associated with discernible differences in CVD risk across various ethnic groups, then our findings will have the potential to influence future research aimed at addressing alternative (and hitherto unexplored) risk factors (such as genetic variation or dietary factors) contributing to excess CVD risk in ethnic minorities. Further offshoots from the TOGETHER research program will not only be able to address some of the novel hypotheses regarding ethnic variation in CVD risk but also serve as a platform for pragmatic randomized controlled trials to explore, for example, various emerging health technologies. One such approach could be leveraging the use of mobile phones/smartphones and applications (apps) to modify risk factors [41] and then identify the key elements to effective and sustainable approaches for reducing the risk of CVD [42]. Furthermore, there could be an opportunity to leverage the derived dataset to perform machine learning techniques, which could be potentially incorporated into creating digital health interventions [43].

As CVD burden varies between population groups and by regions, our study has the potential to investigate the expression of this disease and the contemporary risk factors in a large multiethnic cohort. Thus, our research can be considered a contemporary Framingham study on a large scale. Combining a real-life observational approach with the potential for yearly updates from the EHRs will offer new insights and understanding of the burden of risk factors for re-calibration of the variables used to derive risk prediction tools and dynamic improvement of risk prediction algorithms. Longitudinal follow-up will help quantify the incidence of CVD and, therefore, the derivation of population attributable risk (PAR) [44]. The ability to predict the impact of removing a particular risk factor in specific population groups and the risk of developing subsequent CVD is imperative for service provision and evaluating current public health strategies for CVD risk reduction. Thus, given its sample size, our study will have sufficient power to investigate CVD risk factor burden across diverse ethnicities among NHS Health Check attendees enabling further refinement of guidelines and will therefore have the potential to improve the overall public health of England in the foreseeable future.

The proposed analyses are in keeping with statistical analyses conducted in other similar large-scale population-based studies [45-47]. As the NHS Health Check program collects simple lifestyle-related data, a proportion of the population from this study will be investigated using the NDNS database to derive a more detailed understanding of the impact of nutritional determinants on CVD [48-50]. As this study aims to provide current estimates of CVD risk factor burden in a very large sample of ethnically diverse individuals in London (and following successful linkage with outcomes databases, estimates of association), we believe that this project surpasses every other contemporary study in terms of both its scale as well as representativeness (from an ethnic perspective). While our estimates of association and risk prediction derived from this cohort of CVD-free individuals (at baseline) may be similar to those already obtained from studies conducted in predominantly Western populations, these estimates will nevertheless be significantly refined across diverse ethnicities given the power and precision afforded by the study.

Despite the development of evidence-based guidelines and tools by the NHS, opportunities to reduce CVD mortality and morbidity are still being missed. Premature mortality and high healthcare costs associated with CVD underscore the need for a more detailed investigation into CVD risk across multiple ethnic groups since residual CVD risk remains a major challenge for health systems around the world. With the identification of more than 200 risk factors [51], determining the specific risk factors in population groups is imperative. Therefore, with this study examining an ethnically diverse and contemporary population in London, the findings will have the potential to be applied to other (hitherto under-investigated) ethnicities, and towns and cities around the world that have considerable population diversity. Finally, the systematic approach of linking data from different sources can be utilized by other health systems that have implemented EHRs.

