**Conclusions:**

There is an urgent need for more real-life population health studies based on analyses of routine health data available in EHRs. Findings from our study will help quantify, on a large scale, the contemporaneous burden of CVD risk factors by geography and ethnicity in a large multiethnic urban population. Such detailed understanding (especially interethnic and sociodemographic variations) of the burden of CVD risk and its determinants, including heredity, environment, diet, lifestyle, and socioeconomic factors, in a large population sample, will enable the development of tailored and dynamic (continuously learning from new data) risk prediction tools for diverse ethnic groups, and thereby enable the personalized provision of prevention strategies and care. We anticipate that this systematic approach of linking routinely collected data from EHRs to study CVD can be conducted in other settings as EHRs are being implemented worldwide.

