### Population Prevention Strategy in England

In England, the National Health Service (NHS) established a population-based Health Check program in 2009 to provide a systematic assessment and management of CVD risk for adults. Individuals aged 40-74 years without pre-existing CVD, diabetes, or hypertension are invited for a five-yearly check-up to identify and to receive advice and treatment for their risk of having a CVD event [6]. Commissioned by local authorities and delivered primarily through primary care practices, henceforth referred to as general practices (GP), this program aims to prevent around 2000 deaths and 9500 nonfatal myocardial infarctions (MI) and strokes annually [7,8]. As a free service for all eligible individuals, this program has the potential to reduce health inequalities associated with CVD [7,8], assuming equitable uptake and universal coverage. Available data suggest that between 2011-12, NHS Health Check coverage in east London was quite high at 73% (compared to national coverage of 30%). Of those that attended the screening, over a third belonged to ethnic minority groups such as south Asians and Black African/Caribbeans [9-13]. While modification of individual risk factors (eg, blood pressure) has generally been shown to be associated with improved health outcomes (eg, lower incidence of ischaemic stroke), favorable changes in risk factor distribution at a societal level have also contributed to overall improvements in community health [14]. For example, in 1989, in Poland, the increased accessibility and consumption of fruits and vegetables through the opening of markets resulted in a reduction in CVD mortality [15]. By contrast, Japanese migrants, who adopted the diet and lifestyle of the United States (US) population, relative to those who retained their original dietary patterns, had a higher prevalence of CVD [16]. Given the variation in ethnic-specific diet and lifestyle habits, and given genetic differences across population groups around the world, there is currently an unmet need to understand the complex relationship between ethnicity and factors as diverse as heredity, environment, diet, lifestyle, and socioeconomic factors (and their mutual interaction) in determining the burden, distribution, and temporal trends in both CVD risk factors and clinical CVD outcomes and cause-specific death.

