We developed the following study specific objectives:

To robustly quantify and characterize, across diverse ethnic groups and sociodemographic groups, the burden of CVD risk factors among NHS Health Check attendees in a diverse population in London.To prospectively study the incidence of CVD within this population by EHR linkage.To validate existing CVD risk prediction algorithms and to develop novel, bespoke algorithms for CVD risk prediction among diverse multiethnic population groups.To characterize dietary exposures and nutritional status as well as their associations with CVD outcomes, using data from index assessment methods that mirror or correlate well with those used in national surveillance.

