## Methods

### Study Design and Setting

We propose to conduct a large-scale, cross-sectional observational study of NHS Health Check attendees in London with additional virtual longitudinal follow-up established via electronic health record linkage of their primary (NHS Health Check) and secondary care (hospital) data over 10 years starting in 2009. One of the major providers of EHR software to GP practices is Egton Medical Information Systems (EMIS). GPs utilizing this EHR will be eligible to participate. Figure 1 illustrates the number of individuals belonging to ethnic minority groups within London. Such a high prevalence of diverse ethnic groups in London, relative to other areas in England, coupled with high utilization of the EMIS system (Figure 2), lends itself naturally to London as the ideal backdrop for our proposed investigation.

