### Predictor and Outcome Variables

Cardiovascular risk factors (predictor variables) used to calculate QRISK2 include age, sex, ethnicity, index of multiple deprivations, smoking status, diabetes status, family history of CVD, chronic kidney disease (stage 4 or 5), atrial fibrillation, hypertension treatment, rheumatoid arthritis, lipids, blood pressure, and BMI. EMIS will also extract prescription data. CVD outcomes will include fatal and nonfatal coronary heart disease, fatal and nonfatal stroke, heart failure, all CVD-related hospitalizations (including those for revascularization), and all-cause mortality.

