Additional analyses will be conducted to quantify the impact of factors such as access to healthcare and utilization rates (of NHS Health Checks), prescription rates and medication compliance, and patterns of healthy behavior on CVD risk (both overall and, where possible, within subgroups). Standardized rates of prescription drug use will be calculated to investigate the extent of correlation between the present use of cardiovascular medication and cardiovascular risk. Variations in prescription patterns of CVD prevention and risk factor control, discontinuation of prescribed medication(s), and adverse effects to prescription medications from various therapeutic categories such as anti-hypertensive agents, lipid-lowering drugs (statins), and antidiabetic medication will be further assessed for their impact on CVD as time-dependent covariates in Cox regression models. Physical measurements within the NHS Health Check program will be obtained by the GP practices according to standard operating procedures, anticipating minimum inter-observer variability. Analyses to explore potential sources of heterogeneity concerning physical measurements (besides other characteristics) will also be conducted.

New and existing risk prediction models will be compared in terms of their ability to predict the onset of CVD across diverse population groups to develop improved risk prediction tools for primary prevention of CVD using outcomes data up to 2020. The resulting CVD risk algorithm will be calibrated by further analyses of CVD outcomes data of these patients through to 2027.

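### Diabetes and hypertension burden and PAR from Health Check attendees are not population figures, because the programme does not invite people already diagnosed with either

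*Protocol article*

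**What the plan says.** The Introduction (Population Prevention Strategy in England) gives the programme's invitation rule: "Individuals aged 40-74 years without pre-existing CVD, diabetes, or hypertension are invited for a five-yearly check-up". Study Design and Setting makes the programme's attendees the cohort, describing a "cross-sectional observational study of NHS Health Check attendees in London". Recruitment likewise takes people undergoing Health Checks in consenting practices.

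The first study objective is scoped to match: "the burden of CVD risk factors among NHS Health Check attendees in a diverse population in London". Two later statements are wider. The Abstract's Conclusions promise "the contemporaneous burden of CVD risk factors by geography and ethnicity in a large multiethnic urban population". The Discussion says "Longitudinal follow-up will help quantify the incidence of CVD and, therefore, the derivation of population attributable risk (PAR") and links this to predicting what removing a risk factor would do in particular population groups. The same section describes the cohort as free of CVD at baseline and does not mention diabetes or hypertension.

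Predictor and Outcome Variables lists, among the inputs to QRISK2, "smoking status, diabetes status, family history of CVD, chronic kidney disease (stage 4 or 5), atrial fibrillation, hypertension treatment". Statistical Analyses adds prescribed drugs, "such as anti-hypertensive agents, lipid-lowering drugs (statins), and antidiabetic medication will be further assessed for their impact on CVD as time-dependent covariates".

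**The concern.** PAR depends directly on how common the exposure is in the target population. If people with known diabetes or hypertension are not invited, the cases left among attendees are mainly undiagnosed or newly found disease. A PAR calculated from that remainder describes the attendees. It does not describe London adults aged 40-74, and it does not describe an ethnic group as a whole.

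The Introduction names hypertension and diabetes as underlying factors that may partly explain regional differences in CVD death. The Discussion adds that, if conventional factors do not account for ethnic differences in CVD risk, research should turn to others, such as genetic or dietary ones. Removing diagnosed diabetes and hypertension at entry could contribute to such a finding, because part of the absolute difference between groups has already been taken out. A reader using a PAR for service planning would also give these two factors too little weight.

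**Working it through.** **No figure to reproduce.** The protocol gives no prevalence, diagnosed fraction or PAR for any factor. The inputs below are therefore assumptions, chosen to show direction and rough size.

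**Inputs**
- True prevalence p: 20% in one group, 8% in another (assumed).
- Fraction d of cases already diagnosed and so not invited: 70% to 90% (assumed).
- Relative risk RR: 2 (assumed). The values 1.2 and 1.5, which the protocol's Sample Size section uses for power, are tried afterwards.

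**Formulas**
- Prevalence left among those eligible: p(1 − d) / (1 − pd).
- PAR (Levin): p(RR − 1) / [1 + p(RR − 1)].

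**Prevalence left in the cohort**
- p = 20%, d = 70%: 0.06 / 0.86 = 6.98%.
- p = 20%, d = 90%: 0.02 / 0.82 = 2.44%.
- p = 8%, d = 70%: 0.024 / 0.944 = 2.54%.
- p = 8%, d = 90%: 0.008 / 0.928 = 0.86%.

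**Contrasts between the groups, RR 2**

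| Quantity | Whole population | d = 70% | d = 90% |
|---|---|---|---|
| Prevalence gap (points) | 20 − 8 = 12 | 6.98 − 2.54 = 4.4 | 2.44 − 0.86 = 1.6 |
| Prevalence ratio | 20/8 = 2.50 | 2.74 | 2.83 |
| PAR, high-prevalence group | 0.20/1.20 = 16.7% | 0.0698/1.0698 = 6.5% | 0.0244/1.0244 = 2.4% |
| PAR, low-prevalence group | 0.08/1.08 = 7.4% | 0.0254/1.0254 = 2.5% | 0.0086/1.0086 = 0.9% |
| PAR ratio | 2.25 | 2.63 | 2.79 |

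In the high-prevalence group, PAR is understated by a factor of 16.7/6.5 = 2.6 to 16.7/2.4 = 7.0.

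**Other relative risks, high-prevalence group**
- RR 1.5: 9.1% falls to 3.4% (d = 70%) or 1.2% (d = 90%).
- RR 1.2: 3.8% falls to 1.4% (d = 70%) or 0.5% (d = 90%).

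The proportional understatement is much the same at all three relative risks.

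**Different diagnosed fractions in the two groups.** With d = 90% in the high-prevalence group and 70% in the other, the gap is 2.44 − 2.54 = −0.1 points and the ratio is 0.96. With the fractions reversed, the gap is 6.98 − 0.86 = 6.1 points and the ratio is 8.1. In all four combinations the absolute gap is smaller than the true 12 points, but the ratio can move either way.

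**The case against.** The strongest reply has four parts.

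1. **The exclusion is the programme's, not the study's.** The protocol states no study criterion on diabetes or hypertension; the restriction follows from whom the programme invites. Some attendees may fall outside the rule, and disease found at or after the check can enter, including through the time-dependent drug covariates. This stands, and is why the point says largely removed, not absent.

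2. **PAR is peripheral.** It appears once, in the Discussion, with no factor named, and in neither the objectives nor Statistical Analyses. The rule does not remove smoking, lipids or BMI, and measured blood pressure, a separate predictor, can still vary. This limits the point to diabetes and hypertension. The Discussion still makes the population claim without qualification.

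3. **Burden is already scoped.** The first objective is about attendees, and the Discussion repeats that. This stands; only the Abstract's wider wording needs changing.

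4. **The predictors are listed for scoring.** The list gives what QRISK2 needs, and validating an existing tool requires it. This also stands.

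Stronger readings are tempting but unsupported:
- A reader might infer that the study will re-fit QRISK2. The text speaks of validating existing tools, developing new ones and re-calibrating variables.
- A reader might infer that the two predictors are near-constant and cannot be estimated. The illustration leaves 2.4-7.0% exposed in the high-prevalence group. By Schoenfeld's formula (two-sided 5% assumed), the stated 15,000 events give 99.9% power for RR 1.5 even at 1% exposure in the whole cohort; 4,800 events (200,000 × 2.4%) give 80%. Precision within an ethnic group would be lower, but the clearer limit is which disease the coefficient describes.
- A reader might infer that every ethnic contrast is biased toward zero. That holds for absolute differences here; with equal diagnosed fractions the ratios rise slightly.
- A reader might infer that the C statistic must fall and be misread as QRISK2 failing. No calculation shows this, and the planned ethnic comparisons are made within one cohort under one invitation rule.

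**Conclusion.** The point holds in limited form. On the protocol's own description, attendees come from a programme that does not invite people with diagnosed diabetes or hypertension. The Discussion's PAR statement and the Abstract's burden statement do not carry that restriction. PAR and prevalence for these two factors would understate the population values, by a factor of about 2.6 to 7 for PAR at 20% true prevalence, 70-90% diagnosed and RR 2. Absolute ethnic differences would shrink, from 12 points to 1.6-4.4 with equal diagnosed fractions.

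The direction rests on the invitation rule being broadly followed. The size rests wholly on assumed inputs, including one relative risk for diagnosed and undiagnosed disease. The defect concerns what the study may claim for two factors; the cohort remains usable for its stated objectives among attendees.

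**What to change.** 1. In the Abstract's Conclusions and the Discussion, state burden and PAR as applying to adults attending Health Checks without previously diagnosed CVD, diabetes or hypertension. State also whether any attendees with a prior diagnosis of diabetes or hypertension are in the extract.

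2. Do not report a population PAR for diabetes or hypertension from this cohort alone. Either drop it, or take prevalence by ethnic group from an unrestricted source if one is available.

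3. For any new tool, state that coefficients for diabetes status and hypertension treatment apply to newly identified disease in the eligible population.

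**Cost.** Items 1 and 3 are wording, at the price of a narrower PAR and generalisability claim. The second option in item 2 could cost more. Counts of all registered patients would go beyond the data sharing described under Recruitment, which covers people undergoing Health Checks, and the Results section reports extraction complete by March 2020. Dropping the two PARs avoids that cost.
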